#### Sleep quality.

Participants will be asked to maintain their usual sleep habits over 12 weeks, and they are required to complete the bilingual (English-Chinese) version of the Pittsburgh Sleep Quality Index (PSQI) [89] both before and after the pre-test and post-test sessions. The PSQI is a 19-item self-rated questionnaire for evaluating subjective sleep quality over the previous month. The 19 questions are combined into 7 clinically derived component scores. The Chinese translation of the PSQI is validated for sleep quality assessment in China, possessing robust psychometric properties and high test-retest reliability [90].

#### Gaming behavior.

A simple questionnaire developed by our team will be used to collect information on the participants’ weekly engagement in esports gaming. During the intervention period, we will also ask the players to maintain the same frequency of gaming and gaming habits as before.

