**Objective:**

This study aims to: (1) investigate and compare the long-term effects of 12-week high-intensity interval training (HIIT) and moderate-intensity continuous training (MICT) on various dimensions of esports performance in first-person shooter (FPS) gamers; (2) examine the sustainability of these effects through a 4-week follow-up assessment; and (3) explore the potential associations between physical competence, psychological skills, and gaming performance.

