**Methods:**

In this three-arm randomized controlled trial, 195 FPS gamers (aged 18–29) will be randomly assigned to HIIT, MICT, or control groups. Interventions consist of three weekly sessions for 12 weeks (HIIT: 10 × 1-minute high-intensity bouts interspersed with 1-minute active recovery; MICT: 20-minute continuous moderate-intensity exercise). The primary outcome is flicking capacity (a core metric of esports performance). Secondary outcomes include other gaming operational metrics, esports-related psychological skills, body composition, and physical competence. All outcomes will be assessed at baseline, post-intervention (12 weeks), and follow-up (16 weeks).

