### Research objective

This study aims to investigate the long-term effects of HIIT and MICT on esports performance through a 12-week three-arm randomized controlled trial, and to examine the sustainability of these effects with a follow-up assessment conducted 4 weeks after the intervention cessation. Additionally, we seek to compare the differential impacts of these two exercise modalities on various dimensions of esports performance and to explore their associations with changes in body composition and physical competence, thereby providing evidence-based guidance for esports training regimens and enhancing our understanding of the underlying mechanisms by which different exercise approaches influence esports performance.

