#### Dietary intake.

During the exercise intervention, participants will be instructed to adhere to their regular diet. To evaluate dietary patterns, a validated food diary assessment will be conducted both before and after the intervention [91]. An online nutrition database (http://www.cfs.gov.hk/) will be used to analyze the dietary records [92].

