Participants will be allowed to undertake physical exercise either on a treadmill or outdoors, encompassing exercises such as running, jogging, and brisk walking, provided they reach the stipulated heart rate. To account for the potential confounding effect of the exercise environment (indoor vs. outdoor) [97], we will utilize the built-in GPS tracking feature of the Polar Flow system to record the specific setting of each session. This environmental factor will be considered as a covariate in our subsequent statistical analysis. During the initial three sessions, participants will be obliged to exercise in a laboratory under the guidance and supervision of research staff. This ensures not only a precise understanding and execution of the training regimen but also the safety of participants during subsequent unsupervised exercises. Once it is ascertained that participants can meet the training benchmarks without supervision, they are permitted to carry out their exercises at home in a free-living setting for the remainder of the intervention. During these home-based exercises, participants are required to wear a heart rate monitor to track exercise intensity. The monitor records the exercise data throughout the training program, and with prior consent obtained from participants, we will monitor each participant’s exercise data through the *Polar Flow for Coach*, including metrics such as heart rate, frequency, and running speed to confirm participants’ compliance with the exercise plan. Specifically, we define “adherence” using a dual-criterion approach based on both heart rate compliance and session completion. A single training session will be considered “valid” if the participant meets the specific heart rate prescription: for the HIIT group, achieving the target high-intensity zone for at least 80% of the intervals; for the MICT group, maintaining the target heart rate zone for at least 80% of the continuous exercise duration. Consequently, overall adherence to the exercise protocol is defined as the successful completion of at least 80% of the total prescribed valid sessions. This flexible, home-based research design, combined with remote monitoring, aims to further mitigate participant drop-out rates in longer-term interventions and construct an exercise intervention model that can be implemented long-term in a living environment rather than in a laboratory setting, and the methodological approach has also been employed in prior studies [92,98].

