By comparing multiple exercise modalities against a control condition, this study seeks to identify more effective physical training parameters for enhancing esports performance. The inclusion of follow-up assessments extends beyond immediate effects to examine the duration of exercise-induced benefits after training cessation—a critical consideration for establishing optimal training frequency that allows esports athletes to balance physical training with technical practice time. Furthermore, the larger sample size enables us to draw more reliable conclusions about the differential effects of HIIT and MICT in FPS players, thereby offering more specific data for exercise prescription.

Moreover, several negative health-related consequences have been traditionally associated with excessive screen time and prolonged sedentary behavior in video gamers [100,101]. Excessive sitting time and screen exposure pose potential risks to the health of esports athletes [102,103]. Studies have linked prolonged screen time with lower levels of physical activity and poor cardiovascular health [104,105]. Except for active video games or virtual sports, the majority of video games are typically played in a sedentary position [106]. Should the results of the proposed trial demonstrate that physical exercise effectively enhances esports performance, they could offer a practical rationale for integrating systematic, structured physical training into standard esports regimens. Consequently, while optimizing their competitive outcomes, esports players would concurrently reap the well-established health benefits of regular exercise. This integration would effectively mitigate the health risks associated with prolonged sedentary behavior, exploring a potential dual benefit of enhanced competitive performance and safeguarded occupational health.

The comprehensive approach of this study may contribute empirical data to the ongoing discussion regarding physical training in competitive gaming. These findings could serve as a reference for esports academies and professional teams seeking to incorporate appropriate physical exercise regimens alongside technical and tactical training. By integrating physical exercise into training models, this approach aims to address health concerns that could otherwise undermine the longevity of players’ careers, thereby supporting more sustainable practices within competitive gaming.

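### The habit rules and the dated monitoring end at week 12 and no exercise instruction covers weeks 12 to 16, so the week-16 result cannot be read as benefit after training has stopped

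*Protocol article*

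**What the plan says.** The Abstract gives the second objective as to "examine the sustainability of these effects through a 4-week follow-up assessment". The Research objective section repeats it as "to examine the sustainability of these effects with a follow-up assessment conducted 4 weeks after the intervention cessation". The Significance section goes further: the follow-up is there to "examine the duration of exercise-induced benefits after training cessation", and this is meant to inform how often esports athletes need to train.

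The behaviour rules carry end dates:

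- Gaming: "During the intervention period, we will also ask the players to maintain the same frequency of gaming and gaming habits as before".
- Sleep: "Participants will be asked to maintain their usual sleep habits over 12 weeks". The PSQI is placed around the pre-test and post-test; the follow-up test is not named.
- Diet: the regular-diet instruction applies during the exercise intervention, and "a validated food diary assessment will be conducted both before and after the intervention".
- Exercise: the heart-rate monitor records for the duration of the training program (Intervention section), and staff contact runs over the 12 weeks (Strategies to improve adherence).

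The Data analysis section evaluates changes in diet, physical activity and sleep over the intervention period. Gaming is not on that list. No section says whether HIIT and MICT participants should stop, may continue or should return to their usual activity in weeks 12 to 16, or what controls should do about exercise then.

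**The concern.** A result described as lasting after training cessation requires that training did cease, or at least that it is known who stopped. As written, the exercise arms leave the programme at week 12 with no stated instruction and return at week 16 to be tested. A score still above control could reflect durable adaptation, exercise carried on at home, or a change in gaming.

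The protocol treats these behaviours as threats. The Physical activity and sitting time section says additional aerobic exercise during the intervention could influence the final test, and the Measurements section says lifestyle factors are monitored and standardised to isolate the intervention effect. The same reasoning applies to the last four weeks, which the safeguards do not cover.

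At stake is what the sustainability result may be said to show, and therefore the advice on training frequency that the authors want to draw from it.

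**Working it through.** **Step 1: periods set side by side.**

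| Item | Period stated | Weeks 12–16 covered? |
|---|---|---|
| Gaming rule | Intervention period | No |
| Sleep rule | 12 weeks | No |
| Diet rule | Exercise intervention | No |
| PSQI | Pre-test and post-test | No |
| Food diary | Before and after the intervention | No |
| Heart-rate recording | Training program | No |
| Lifestyle-change check | Intervention period; gaming not listed | No |
| IPAQ | No time points given | Unknown |
| Gaming questionnaire | Weekly engagement; no time points given | Unknown |
| Exercise instruction after week 12 | None stated | No |
| Outcome assessment | Baseline, week 12, week 16 | Yes |

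Outcomes reach week 16; no dated rule or dated monitoring item does. The Abstract says all outcomes are assessed at 16 weeks, but the Measurements section places control and monitoring variables in a category of their own. If the Abstract is meant to include them, it conflicts with the narrower timing given for the PSQI and the food diary.

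**Step 2: how large the ambiguity can be.** The plan has no figure of its own to reproduce here, so this is an illustration. Write the week-16 contrast with control, in SD units, as

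contrast = L × (1 − c) + E × c + s

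where L is the lasting effect in those who stop, E the effect in those who continue, c the share who continue, and s any net between-arm shift from gaming or other behaviour. E = 0.4 is the planning effect size in the Experimental design section, used only for scale. L, c and s are assumptions; the document gives no value for them.

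With L = 0 and s = 0:

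- c = 0%: 0.4 × 0 = 0.00
- c = 25%: 0.4 × 0.25 = 0.10
- c = 50%: 0.4 × 0.50 = 0.20
- c = 75%: 0.4 × 0.75 = 0.30

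With L = 0.2, c = 0% and s = 0: 0.2 × 1 + 0.4 × 0 = 0.20.

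The third and last cases give the same 0.20 SD. In one, nothing lasts after stopping; in the other, half of the effect does. Outcome scores alone cannot tell them apart. A shift s of ±0.1 moves every value by ±0.1.

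**Step 3: can adjustment rescue it?** Not cleanly. Exercise and gaming in weeks 12 to 16 are chosen after randomisation and may themselves depend on the assigned arm. Entering them as covariates would not recover the effect that would be seen had everyone stopped. They can inform interpretation.

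**The case against.** **The second objective is answered anyway.** Outcomes are measured in all three randomised arms at week 16, with intention-to-treat as the primary approach. That comparison validly shows whether group differences persist four weeks after the programme ends, whatever participants then do. This stands. A reader might infer that the objective goes unanswered or that the comparison is biased; the document does not support that. Continuing to exercise is a consequence of assignment, so it changes what the contrast means without invalidating it.

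**Activity and gaming may be recorded at week 16.** This also stands. The IPAQ and gaming questionnaire have no stated end date, the Experimental design section says all groups report these behaviours without a limit, and the schedule figure is not shown. It would be wrong to say that no such data will exist.

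**VO2max is a week-16 outcome.** The 20-m PACER gives partial objective information on detraining. Retained fitness and continued training can look alike, however, so it does not settle the question.

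**A rebound in gaming is speculative.** Sessions take 3 × (3 + 20 + 3) = 78 minutes a week, and 78/300 = 26% of the five-hour eligibility minimum. That is a ceiling: it assumes all freed time goes to gaming. Players are asked to keep gaming constant during the intervention, so under the protocol this time was not taken from gaming, and Aim Lab was chosen to limit gains from practice in players' own games. The point does not need a rebound; continued exercise is enough.

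**Nothing shows that many will continue.** Participants have no regular exercise habit at entry and receive reminders and a voucher. The aim to "construct an exercise intervention model that can be implemented long-term in a living environment" explains home-based delivery; it does not say participants are expected to carry on after week 12. Hence c is an assumption, and the illustration is not a forecast.

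**A condensed article may leave follow-up conduct to the full protocol.** Partly fair for the missing exercise instruction. It does not cover the rules and measurements to which this text attaches an explicit earlier end.

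**Conclusion.** The point holds in limited form. The gaming, sleep and diet rules, the dated PSQI, food-diary and heart-rate monitoring, and the lifestyle-change check all end with the intervention, and no instruction on exercise is stated for weeks 12 to 16. The week-16 contrast is therefore sound as the effect of having been assigned the programme, but it does not identify the duration of benefit after training has stopped.

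The size cannot be fixed from the document. With E = 0.4 and no lasting effect, assumed continuation of 25% to 75% produces an apparent persisting difference of 0.10 to 0.30 SD. The conclusion needs only that some exercisers might continue, or change their gaming, unrecorded; it does not depend on any particular share. The primary comparison at week 12 is not affected.

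**What to change.** 1. Extend the existing keep-usual-habits rules for gaming, sleep and diet to week 16 in all three arms.
2. State what participants are asked to do about structured exercise in weeks 12 to 16, and reconcile that with the word cessation in the Research objective and Significance sections. Which instruction to give is for the investigators.
3. At the week-16 visit, add the PSQI (its previous-month window, as the protocol describes it, matches this period) and one question on the number of structured exercise sessions since week 12. Add the IPAQ and the gaming questionnaire, or confirm them if already scheduled.
4. Extend the lifestyle-change check to weeks 12 to 16 and add gaming to it. Report these data by arm for interpretation; do not present covariate adjustment for them as isolating the lasting effect. A repeat food diary is needed only if diet is to be part of the extended check.
5. State what week 16 estimates. Describe an effect as sustained after cessation only if the recorded behaviour supports it; otherwise report the 16-week effect of assignment to the programme.

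The cost is a change of wording and a few more minutes of questionnaires, mostly ones already in use, at a visit already planned. The drawbacks are slightly more participant burden and reliance on self-report. Data on weeks 12 to 16 would be hard to reconstruct later, so this should be settled before participants reach week 12.

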#### Dietary intake.

During the exercise intervention, participants will be instructed to adhere to their regular diet. To evaluate dietary patterns, a validated food diary assessment will be conducted both before and after the intervention [91]. An online nutrition database (http://www.cfs.gov.hk/) will be used to analyze the dietary records [92].

### Intervention

From previous literature, it has been observed that a HIIT protocol involving 10 × 1-minute bouts at 80–90% of maximum heart rate (HRmax) with 1-minute recovery periods at 40–50% of HRmax is deemed effective [92–94]. Moreover, this intensity and interval have shown significant short-term effects on esports performance in previous studies [27]. This study will follow this protocol for the HIIT exercise group. MICT in this study will consist of continuous exercise at 64–76% of HRmax for 20 minutes, ensuring that the total exercise duration is equivalent to the HIIT protocol to maintain comparable training volumes between groups. A standardized 3-minute warm-up with dynamic stretching and a 3-minute cool-down at 50% HRmax will be added at the beginning and end of each exercise session for both intervention groups. Participants in both intervention groups will be required to complete their respective exercise protocols three times per week throughout the 12-week intervention period. Real-time heart rate monitors (Polar Pacer) will be used to ensure intensity during exercise sessions. In addition, a rating of perceived exertion (RPE) will be employed in each training session utilizing the 6–20 Borg scale [95]. During high-intensity intervals, participants will be instructed to maintain an RPE between 15–18, while during the low-intensity intervals, warm-up, and cool-down phases, an RPE of 11–13 will be targeted [96]. For the MICT group, participants will maintain a moderate-intensity effort corresponding to an RPE of 12–14 throughout the continuous exercise session. Meanwhile, all training sessions will be guided by a professional fitness trainer who will ensure the professionalism and safety of the entire exercise process.

Participants will be allowed to undertake physical exercise either on a treadmill or outdoors, encompassing exercises such as running, jogging, and brisk walking, provided they reach the stipulated heart rate. To account for the potential confounding effect of the exercise environment (indoor vs. outdoor) [97], we will utilize the built-in GPS tracking feature of the Polar Flow system to record the specific setting of each session. This environmental factor will be considered as a covariate in our subsequent statistical analysis. During the initial three sessions, participants will be obliged to exercise in a laboratory under the guidance and supervision of research staff. This ensures not only a precise understanding and execution of the training regimen but also the safety of participants during subsequent unsupervised exercises. Once it is ascertained that participants can meet the training benchmarks without supervision, they are permitted to carry out their exercises at home in a free-living setting for the remainder of the intervention. During these home-based exercises, participants are required to wear a heart rate monitor to track exercise intensity. The monitor records the exercise data throughout the training program, and with prior consent obtained from participants, we will monitor each participant’s exercise data through the *Polar Flow for Coach*, including metrics such as heart rate, frequency, and running speed to confirm participants’ compliance with the exercise plan. Specifically, we define “adherence” using a dual-criterion approach based on both heart rate compliance and session completion. A single training session will be considered “valid” if the participant meets the specific heart rate prescription: for the HIIT group, achieving the target high-intensity zone for at least 80% of the intervals; for the MICT group, maintaining the target heart rate zone for at least 80% of the continuous exercise duration. Consequently, overall adherence to the exercise protocol is defined as the successful completion of at least 80% of the total prescribed valid sessions. This flexible, home-based research design, combined with remote monitoring, aims to further mitigate participant drop-out rates in longer-term interventions and construct an exercise intervention model that can be implemented long-term in a living environment rather than in a laboratory setting, and the methodological approach has also been employed in prior studies [92,98].

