### Strategies to improve adherence

Firstly, before enrollment, we repeatedly confirm the participants’ willingness and compliance with the study’s requirements. Secondly, dedicated researchers will be responsible for monitoring the intensity and frequency of the participants’ weekly exercise through the *Polar Flow for Coach* system, and they will repeatedly remind and guide them to complete the 12-week training plan as required. At the same time, the researchers will maintain contact with the participants over the 12 weeks and collect their daily dietary records. Thirdly, participants will receive a supermarket voucher valued at HK$200 upon completion of the intervention.

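### RPE 12–13 is assigned both to HIIT recovery and cool-down (at most 50% HRmax) and to MICT (64–76% HRmax)

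*Protocol article*

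**What the plan says.** All the relevant text is in the Intervention section of the protocol article.

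- **HIIT recovery, heart rate.** The literature protocol is described as 1-minute bouts at 80–90% of HRmax "with 1-minute recovery periods at 40–50% of HRmax is deemed effective", and the next sentence but one adopts it for the HIIT arm.
- **Cool-down, heart rate.** In both exercise arms "a 3-minute cool-down at 50% HRmax will be added".
- **Recovery and cool-down, RPE (Borg 6–20).** Bouts are run at RPE 15–18, "while during the low-intensity intervals, warm-up, and cool-down phases, an RPE of 11–13 will be targeted".
- **MICT, heart rate.** "MICT in this study will consist of continuous exercise at 64–76% of HRmax for 20 minutes".
- **MICT, RPE.** "participants will maintain a moderate-intensity effort corresponding to an RPE of 12–14 throughout the continuous exercise session".

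The same section says what counts as a valid session. The criterion is heart rate: "for the HIIT group, achieving the target high-intensity zone for at least 80% of the intervals"; for MICT, time in the target zone. RPE does not enter it. Home sessions are monitored remotely, "including metrics such as heart rate, frequency, and running speed to confirm" compliance. Under Strategies to improve adherence, "dedicated researchers will be responsible for monitoring the intensity and frequency of the" participants' weekly exercise.

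**The concern.** Each low-intensity phase has two targets, one in heart rate and one in perceived exertion, and the protocol's own MICT pairing suggests that the two do not describe the same effort. In the MICT arm a rating of 12 or 13 belongs to 64–76% of HRmax. In HIIT recovery and in the cool-down the same ratings stand beside 40–50% and 50%.

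This bears on what the HIIT arm receives. HIIT is defined by the alternation of hard and easy minutes, and recovery is 10 of the 20 minutes of the main set. Comparing HIIT with MICT is a stated objective, and the protocol fixes equal exercise duration so that training volume is similar. If recovery is steered by RPE 12–13 and lands near MICT intensity, the arms differ less in pattern than intended. Only the first three sessions must take place in the laboratory. With 3 × 12 = 36 sessions prescribed, up to 36 − 3 = 33 may be done at home, where participants pace themselves.

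**Working it through.** The plan gives no figure of its own to reproduce here. The check sets its stated pairs side by side. The Introduction describes MICT in general at a lower band (40–60%); I use the trial's own prescription from the Intervention section.

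| Phase | % HRmax | RPE |
|---|---|---|
| HIIT bout | 80–90 | 15–18 |
| MICT | 64–76 | 12–14 |
| HIIT recovery | 40–50 | 11–13 |
| Cool-down, both arms | 50 | 11–13 |

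**Step 1: overlap in RPE.** {11, 12, 13} and {12, 13, 14} share {12, 13}. RPE 11 is not shared.

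**Step 2: gap in heart rate.** Top of recovery to bottom of MICT: 64 − 50 = 14 points. Cool-down to bottom of MICT: 64 − 50 = 14 points. Recovery and MICT midpoints: 70 − 45 = 25 points. The RPE ranges overlap and the heart-rate bands do not. Steps 1 and 2 need no assumption about how RPE converts to heart rate.

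**Step 3: what it could mean for the HIIT session (illustration).** Assume that a rating means the same heart rate in recovery as in MICT, that the relation is linear within the MICT band, and that each minute is spent at its target. Then RPE 12 = 64%, RPE 14 = 76%, so RPE 13 = 70%. Take bouts at their midpoint, 85%.

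- Bout-to-recovery difference, heart-rate target followed: 85 − 50 = 35 to 85 − 40 = 45 points.
- Bout-to-recovery difference, RPE 12–13 followed: 85 − 70 = 15 to 85 − 64 = 21 points.
- Mean main-set intensity, heart-rate target (midpoint 45%): (85 + 45)/2 = 65%.
- Mean main-set intensity, RPE 12–13: (85 + 64)/2 = 74.5% to (85 + 70)/2 = 77.5%.
- MICT midpoint: 70%.

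On these assumptions the choice of target moves mean HIIT intensity from about 5 points below MICT to about 5–8 points above it. Heart rate lags within a 1-minute recovery, so these are upper-end illustrations, not expected values.

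**Step 4: how far RPE 11 resolves it.** Extending the line through the two midpoints (70%, RPE 13) and (85%, RPE 16.5) gives a slope of 3.5/15 = 0.233 RPE per point. RPE 11 then falls at 70 − 2/0.233 ≈ 61%, and 50% of HRmax at 13 − 0.233 × 20 ≈ RPE 8.3. This goes below both stated pairs, so I do not rest the point on it. It only suggests that a revised range should end at 11 rather than start there.

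**The case against.** Four arguments can be made on the other side.

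1. *The protocol gives no RPE-to-heart-rate conversion, and the situations differ.* MICT's 12–14 describes 20 continuous minutes; the recovery rating describes single minutes straight after hard bouts, when perceived exertion may stay raised. This is a fair explanation for part of the recovery mismatch. It does not cover the cool-down, which carries the same RPE range at 50% of HRmax, lasts 3 minutes and is standardised across both arms, so MICT participants do it without any preceding bouts. The RPE sentence could be read as meant for HIIT only, since MICT is named in the next one, but it does not limit its cool-down target to one arm.

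2. *Both targets can be met.* A reader might infer that the two instructions are incompatible. They are not across the whole range: RPE 11 lies inside 11–13 and outside MICT's 12–14. The clash is at 12 and 13.

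3. *Heart rate governs.* A reader might also infer that the recovery prescription is left undetermined. The text points the other way: monitors are there to secure intensity, RPE is added to them, and session validity is a heart-rate rule. This stands. The prescription is inconsistent, not open.

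4. *The adherence rule.* Because it scores only the bouts, a reader might infer that a hard continuous run without recovery would pass as HIIT and that the rule needs a recovery check. The documents do not support making that a defect. The rule presupposes an interval session and catches the easier shortfall: a session held at 64–76% never reaches the 80% floor. Holding 80–90% for 20 minutes is harder than what is prescribed, in people recruited for not exercising regularly, and it would have to go unnoticed under remote monitoring and weekly review. The rule feeds only a per-protocol sensitivity analysis.

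**Conclusion.** The inconsistency is real but limited. Two of the three whole-number ratings given for recovery and cool-down also belong to MICT, at heart rates at least 14 points higher. That follows from the stated ranges alone.

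The possible effect on the HIIT–MICT contrast (a bout-to-recovery difference of 15–21 points in place of 35–45) rests on carrying the MICT pairing over to recovery, on linearity within the band, and on participants following RPE 12–13 rather than the monitor. The documents do not say how many would, and no effect on any estimate is shown. Because heart rate appears to be the governing measure, many may not be misled.

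The intention-to-treat analysis and the definition of a valid HIIT session can stay as they are. What needs correcting is the prescription.

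**What to change.** In the Intervention section, state that 40–50% of HRmax for recovery and 50% for cool-down are the governing targets. Lower the RPE range for these phases so that it ends at 11 or below, under MICT's 12–14. If RPE 11–13 is what the investigators intend, restate the recovery and cool-down heart-rate bands to match it. Either way, each phase should carry one consistent pair.

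No recovery criterion, such as a required drop in running speed, needs to be added to the adherence definition.

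The cost is a small change to what participants and trainers are told. Sample size, outcomes and analysis are untouched.
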